### Progression criteria

The feasibility study will progress to a full study unless there is:Failure by more than 40% of participants to provide reliable data for daily determination of time spent in moderate to vigorous exerciseFailure by more than 40% of participants to maintain engagement with the intervention.Failure to identify less than 80% of the required number of peer mentors by the LSP tutors in a timely fashion.

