**Methods:**

The trial is set in eight Local Sports Partnership (LSP) hubs that have structured physical activity programmes. The hubs are the units of randomisation (clusters), and individuals are the units of analysis (participants). Eligible participants will contact one of the hubs, with each hub running four physical activity programmes. Each programme requires between 12–15 inactive adults, resulting in 48–60 participants per hub. Allowing for 20% dropout rate, an additional 96 people will be recruited giving a maximum sample of 576. The hub will be randomised: true control, usual programme or MFL intervention. The true control group will be given information about physical activity but will not be included in a programme for the duration of the trial; the intervention will involve the instructor training one (or more) of the participants to be a peer mentor using an educational toolkit; and usual care groups will have physical activity classes delivered as normal. Baseline data will collect physical activity measures and follow-up measurements will be obtained at 3 and 6 months. All participants will be asked to wear a device for measuring activity on the thigh (activPAL) for 7 days before commencing the programme and at 3 and 6 months. The primary objective of the study is to investigate if it is feasible to deliver the intervention and collect data on moderate to vigorous physical activity (MVPA) on all participants, thereby providing valuable information to guide sample size calculation for a future, more definitive trial.

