### Study design

Move for Life is a feasibility cluster randomised control trial (RCT) where the LSP hubs are the units of randomisation (the clusters), and individuals within the hubs are the units of analysis (the participants). The advantage of a cluster RCT is that it overcomes contamination problems that arise if a simple random allocation is used. When testing a complex intervention, randomisation of participants risks contamination if individuals from both arms attend the one group. This study will enrol a total of eight hubs and randomise physical activity groups to each of three arms. This framework is in line with the recommendations of Eldridge et al. [20] and the CONSORT [19] guidance on the minimum number of clusters required to obtain accurate estimates of rates and proportions in pilot and definitive cluster RCTs, respectively. The first arm is the Move for Life intervention (three hubs), the second is the usual programme (three hubs) and the third is the true control (two hubs).

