It was initially envisaged that the Local Sports Partnerships (LSP) tutors would identify a suitable non-professional volunteer from existing programmes to act up as a peer mentor for this study. The desirable criteria were strong motivation and interpersonal skills and experience with group dynamics. However, because of challenges recruiting in this way and concerns about upsetting the group with an ‘outsider’ as a peer mentor, it was decided to recruit the peer mentor from the groups during the trial. Part of the role of the LSP tutor facilitating the programme would be to identify participants suitable for the peer mentor role*.*

A team of educational experts with experience in physical activity and behavioural change will provide the peer mentor training through a series of interactive workshops. The peer mentors will be identified by the LSP sports development officer in the early stages of the Move for Life trial and will receive training during the course of the programme. They will be trained in motivational change techniques so that they will be able to develop rapport with their peers and to support and encourage them in their journey to become more physically active. They will be trained on group dynamics, how to access local assets and facilities, to access funding by applying for grants and to promote their group by social and local media so as to secure the sustainability of the programme. During the trial, they will have the support of the sports development officer and, thereafter, peer mentors will be provided with leadership training courses and linked with local community organisations, including the LSPs.

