## Discussion

Participant recruitment is an essential consideration for the MFL feasibility study. Accordingly, several meetings were held to develop the recruitment strategy. The important questions were what strategies to use for recruitment, what days and times would best suit potential participants for recruitment events and how long before the commencement of the trial should recruitment begin. Further challenges envisaged regarding recruitment are that it may be difficult to attract older adults under the age of 60 years who may be working and who may not identify as being ‘older adults’.

It may be difficult to appeal to all these age groups using the same recruitment strategy, terminology and imagery. Furthermore, it may be difficult to convince health care professionals that the interventions are safe and effective for their patients and that may present a recruitment challenge. Consequently, we have involved clinical members of the research team in the recruitment.

There were also questions about numbers of physical activity programmes within each hub and if adequate numbers were not found to run a particular type of programme, what would happen. The team agreed that all hubs would not necessarily have the exact same number of programmes (some may run with three and others with four, depending on demand). There was also the question of participant preference regarding physical activity programmes. The team agreed that at the screening event, participants would be asked to rank the activity programmes in order of preference and they would be advised that they could not be guaranteed their first preference but every effort would be made to accommodate them.

There were several other points of concern for the research team. Ideally, there would have been stratification in the randomisation process in terms of hub profile: social status, age and gender. After discussion with feasibility trial experts, the team decided to stratify along urban-rural lines only. In Limerick, there are two urban and two rural hubs and, in Clare, there are two rural and two urban hubs. The research analysis team will be blinded. It will be necessary to be aware of concealment at meetings and to conceal information regarding the hubs from the analysis team.

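### The third progression criterion is inverted by a double negative: taken literally, it blocks the full trial when enough peer mentors are identified

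*Protocol article*

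**What the plan says.** The section on progression criteria makes progression the default: "The feasibility study will progress to a full study unless there is" one of three listed conditions. The first two are that more than 40% of participants do not supply reliable activity data, and that more than 40% do not stay engaged with the intervention. The third is "Failure to identify less than 80% of the required number of peer mentors by the LSP tutors in a timely fashion". No other part of the article restates the mentor threshold or corrects its direction.

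On who identifies the mentors, the section on development of the intervention first makes this part of the LSP tutor's role. Its next paragraph says "The peer mentors will be identified by the LSP sports development officer in the early stages of the Move for Life trial". The progression criterion names the tutors.

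The article gives no figure for the required number of mentors. The abstract says "the intervention will involve the instructor training one (or more) of the participants to be a peer mentor", which leaves the number per group open. The study design section assigns three hubs to the intervention arm, and the discussion says of programmes per hub that "some may run with three and others with four, depending on demand".

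**The concern.** Each listed item is a reason not to progress, so each should describe a failure. The third combines three reversing terms: the *unless* that opens the list, *failure to*, and *less than*. The last two cancel, and what remains describes success. A reader who applies the sentence as written would hold back the full trial because mentors had been found.

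This is one of only three go/no-go rules and the only one about identifying mentors, the component that the trial's title singles out. It may also matter in practice: the section on development of the intervention reports that the first plan for finding mentors ran into difficulty and was replaced. A progression rule is set in advance so that the decision does not depend on interpretation once results are known. Here the team must set aside its own wording to reach a sensible decision.

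**Working it through.** The plan states no figure that can be reproduced for this point. The check is one of logic, followed by an illustration.

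**Inputs**
- Direction: progress unless a listed condition is true (progression criteria).
- Threshold: 80% of the required number (third criterion).
- Intervention hubs: 3 (study design).
- Programmes per hub: 3 or 4, and hubs may differ (discussion).
- Mentors per group: one. This is an assumption, since the abstract allows one or more.

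**Logic.** Let *m* be the number of mentors identified in time and *R* the required number.
- Literal reading: block if NOT (*m* < 0.8*R*), that is, if *m* ≥ 0.8*R*.
- Reading in line with the first two criteria: block if *m* < 0.8*R*.

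These two conditions are exact complements, so they give opposite results at every *m*, whatever *R* is.

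The sentence can also be parsed with 80% as the share *not* identified. It then blocks if (*R* − *m*) < 0.8*R*, that is, if *m* > 0.2*R*. This too blocks when many mentors are found and passes when few are, so the other parse does not rescue the wording.

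**Comparison with the first two criteria.** Each of these states one failure and an upper limit on it (more than 40%). More failure leads to blocking, which is the sensible direction. The third sets *failure* beside a lower limit, and that turns it round.

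**Illustration.** With one mentor per group, *R* lies between 3 × 3 = 9 and 3 × 4 = 12. Because hubs may differ, 10 and 11 are also possible.

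| *R* | 0.8*R* | As written: blocks at *m* | As written: passes at *m* | Corrected: blocks at *m* | Corrected: passes at *m* |
|---|---|---|---|---|---|
| 9 | 7.2 | 8–9 | 0–7 | 0–7 | 8–9 |
| 10 | 8.0 | 8–10 | 0–7 | 0–7 | 8–10 |
| 11 | 8.8 | 9–11 | 0–8 | 0–8 | 9–11 |
| 12 | 9.6 | 10–12 | 0–9 | 0–9 | 10–12 |

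With 12 groups, for example, finding no mentors passes the criterion as written and finding all 12 blocks it.

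**The case against.** The strongest reply is that nobody would apply the literal text. The first two criteria show which way the rule is meant to run, the 80% figure is not in doubt, and nothing in data collection, analysis or the care of participants depends on the wording. All of that stands, and it makes this a drafting error. It does not make the sentence right: the rule is stated in full in the article and is wrong as stated, so it is not a detail left to a fuller document.

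A reader might infer that the design fixes the required number of mentors, at 12 for instance, and that leaving it out is a further fault. The documents do not support this. The number per group is open, hubs may run three or four programmes, and the article says that details of the intervention were still being completed. A figure of this kind may also sit in the full protocol. The same holds for the exact time by which mentors must be found.

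The inconsistency over tutor and sports development officer is real, but it has no bearing on the inversion. It would change the count only if one role's identifications alone were allowed to count, and the article does not say so.

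**Conclusion.** The point holds. As written, the third criterion blocks progression when 80% or more of the required mentors are identified and does not block it when fewer are. The reversal is complete for this criterion and rests on no assumption about the required number. Only the illustrative counts depend on one mentor per group and 9 to 12 groups.

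Two stronger readings should be avoided. One is that the team intended to stop on success, or that the actual decision would be reversed; the neighbouring criteria point the other way. The other is that a shortage of mentors would by itself carry the study forward; it would only pass this one criterion, and the other two could still block. The wording should be corrected before the criterion is applied.

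**What to change.** In the third progression criterion, change *less than* to *at least*, so that the blocking condition is failure to identify at least 80% of the mentors required, in a timely fashion. An equivalent form drops *failure to* and makes identification of less than 80% the blocking condition. Either is a one-phrase edit that needs no new data and leaves the threshold as it is. The counts in the table need not be written into the rule.

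As a secondary edit, reconcile the section on development of the intervention, which names the LSP tutor and then the LSP sports development officer, with the progression criterion, which names the tutors. That costs one further sentence.

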### Data collection

The data collection team will conduct the physical tests, apply the activPAL device and facilitate completion of a questionnaire by all participants. After eligibility has been confirmed and informed consent has been obtained, MFL participants will complete a questionnaire comprising of four modules: behavioural change techniques, well-being; healthcare resource use and out-of-pocket expense and demographics (Additional file 3). They will then undergo a set of physical health assessments, including body mass index (BMI) and waist circumference. Validated tests of functional ability including balance and strength testing will be carried out including grip strength and the TUG test. Other parameters for testing include physical function (6-min walk test), falls risk and dual-task ability (dual-task timed up and go test), stand balance (single leg stand) and lower body strength (single and repeated chair to standing).

Physical activity outcomes (MVPA and daily sedentary time) will be measured using the activPAL, a small (9 g) device worn on the thigh. This device adheres to the right thigh, protected by a waterproof dressing. Participants will be asked to wear it continuously for seven days, and it will record physical activity and body posture (sitting, lying, standing or walking) via tri-axial accelerometer technology. The device has been selected because it records both activity and sedentary time with a high degree of accuracy, and it is well tolerated, producing long continuous wear periods [37, 38]. Data will be processed to identify daily time in bed (detected by a proprietary algorithm), daily standing time, daily time spent sedentary, daily time spent in light physical activity and in moderate to vigorous physical activity. Time spent in light and moderate to vigorous activity will be derived from the triaxial accelerometer data using the cut points validated by Powell et al. [39]. These additional behaviours may impact health in an older population. The testing team who take measurements and process accelerometer data will be blinded as to the trial status of each cluster.

Additional file 2 contains the entire testing protocol that will be carried out at baseline, immediately after testing and 3 months post intervention. Information for the process evaluation will be collected on an ongoing basis during the study (Fig. 3).

**Fig. 3 Fig3:**
[figure not shown]
Timeline for the Limerick hubs

Interviews of stakeholders involved in previous physical activity programmes were conducted between January and March in order to inform the intervention development. From January to April, the team has developed the intervention. The trial commences in May and 8 weeks before commencing, and recruitment strategies have been developed. Four weeks beforehand, information sessions will take place. The trial will commence with recruitment, enrolment and baseline testing in Limerick hubs in May until July and in Clare from August until October. Follow-up testing at 3 and 6 months will follow for the hubs in Limerick and Clare.

### Analysis plan

As this is a feasibility study, the analysis will focus on confidence interval estimation. Accordingly, any hypothesis testing or regression modelling will be considered entirely exploratory in nature. Demographics and baseline characteristics of all randomized participants will be summarized for each group as well as overall. Continuous variables will be reported as mean ± standard deviation. Categorical variables will be reported as *n* and percentage. The research team analysing the data will be blinded as to the affiliation of each hub. An exploratory analysis of cost-effectiveness, in terms of estimated cost and quality-adjusted life years (QALYs), will be presented.

### Qualitative analysis

After the trial, a subsection of participants will be interviewed to investigate strengths, weaknesses and factors for scalability. This will form part of a mixed methods approach to evaluate the application of MFL and to understand its potential to impact public health on a national level. A process evaluation questionnaire as well as in-depth semi-structured exit interviews with a subsample of intervention participants and stakeholders will be conducted. Recruitment for the interviews will be purposive and sampling will continue until no new themes or categories emerge from the data. Participants will be asked whether they liked the programme and perceived it to be effective and whether the programme language was acceptable and understandable and their perceptions of the professional instructors and assistants evaluated. Interviews will be digitally recorded and transcribed. NVIVO version 11, a qualitative research software package, will be used to assist the analysis of the data with thematic analysis [40] used to analyse the finding.

## Discussion

Participant recruitment is an essential consideration for the MFL feasibility study. Accordingly, several meetings were held to develop the recruitment strategy. The important questions were what strategies to use for recruitment, what days and times would best suit potential participants for recruitment events and how long before the commencement of the trial should recruitment begin. Further challenges envisaged regarding recruitment are that it may be difficult to attract older adults under the age of 60 years who may be working and who may not identify as being ‘older adults’.

It may be difficult to appeal to all these age groups using the same recruitment strategy, terminology and imagery. Furthermore, it may be difficult to convince health care professionals that the interventions are safe and effective for their patients and that may present a recruitment challenge. Consequently, we have involved clinical members of the research team in the recruitment.

There were also questions about numbers of physical activity programmes within each hub and if adequate numbers were not found to run a particular type of programme, what would happen. The team agreed that all hubs would not necessarily have the exact same number of programmes (some may run with three and others with four, depending on demand). There was also the question of participant preference regarding physical activity programmes. The team agreed that at the screening event, participants would be asked to rank the activity programmes in order of preference and they would be advised that they could not be guaranteed their first preference but every effort would be made to accommodate them.

There were several other points of concern for the research team. Ideally, there would have been stratification in the randomisation process in terms of hub profile: social status, age and gender. After discussion with feasibility trial experts, the team decided to stratify along urban-rural lines only. In Limerick, there are two urban and two rural hubs and, in Clare, there are two rural and two urban hubs. The research analysis team will be blinded. It will be necessary to be aware of concealment at meetings and to conceal information regarding the hubs from the analysis team.

The trial will have staggered commencement which is not unusual for a cluster feasibility trial but may have a seasonal effect. It is anticipated that the shorter daylight hours in Ireland from November to February could impact on the outcomes of hours of physical activity and sedentary time especially with regard to follow-up testing which will be in September for some and in mid-winter for later starters. Using freely accessible online data [41], the results will be correlated to the number of daylight hours.

The study will generate important data relating to recruitment and retention of participants; concealment of randomisation; and acceptability and appropriateness of intervention components, data collection and factors for analysis. The data will determine if a larger RCT is possible and will inform the research team of important considerations when planning a trial of larger magnitude.

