### Randomisation process

The hubs will be the unit of randomisation and will be randomised to each arm. Each hub (cluster) will be geographically separated to reduce contamination effect. Clusters will be stratified as rural or urban. Hubs will be randomised to one of the following: true control (two hubs), usual programme (three hubs) or MFL intervention (three hubs). Participants in the true control group will be given information about physical activity but will be placed on a waiting list for access to the MFL physical activity programmes for the duration of the trial. They will be offered the programmes after the trial. The participants allocated to the MFL intervention group and the usual physical activity programmes will not be aware of their status. Randomisation will only occur and will only be revealed to participants and their instructors after all the baseline data have been collected.

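### County fixes the season of every visit but is not a stated randomisation stratum, and the timing of randomisation does not clearly fit the staggered start

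*Protocol article*

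**What the plan says.** Study design: "This study will enrol a total of eight hubs". Randomisation process: hubs go to "true control (two hubs), usual programme (three hubs) or MFL intervention (three hubs"), and "Clusters will be stratified as rural or urban". The Discussion adds that, after social status, age and gender had been considered as further factors, "the team decided to stratify along urban-rural lines only". It gives the layout: "In Limerick, there are two urban and two rural hubs and, in Clare, there are two rural and two urban hubs".

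The timeline text under Data collection places recruitment, enrolment and "baseline testing in Limerick hubs in May until July and in Clare from August until October", with follow-up at 3 and 6 months in both counties.

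The Discussion acknowledges that the staggered start may bring a seasonal effect. It expects short winter days to affect physical activity and sedentary time, and places follow-up in September for some participants and in mid-winter for later starters. The only stated response is that "the results will be correlated to the number of daylight hours".

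On timing, Randomisation process states: "Randomisation will only occur and will only be revealed to participants and their instructors after all the baseline data have been collected".

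**The concern.** The two baseline windows do not overlap, so county and calendar season coincide at every visit. An arm whose hubs all fall in one county has its change in MVPA and sedentary time, and possibly its retention, measured in a different season from hubs in the other county. The protocol names the seasonal influence, yet the stated allocation rule does not guard against it. A correlation of results with daylight hours describes an association; it does not take season out of a comparison between arms.

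There is also a question of sequence. If randomisation waits for the last baseline visit of the whole trial, it waits for Clare, whose baseline runs to October. By then some follow-up is already expected.

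At stake are the between-arm estimates with confidence intervals, including those for retention and attendance, that are meant to inform a later trial.

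**Working it through.** **Inputs from the protocol article.** 8 hubs; arms of 3 MFL, 3 usual programme and 2 true control (Randomisation process); 2 urban and 2 rural hubs in each county (Discussion); Limerick baseline May-July, Clare August-October, follow-up at 3 and 6 months (timeline text). The counts agree: 3 + 3 + 2 = 8, and 2 × (2 + 2) = 8.

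**Assumption.** The article does not say how 3:3:2 is divided between the two urban-rural strata of four hubs. I take one control hub in each, with 2 MFL and 1 usual programme in one stratum and the reverse in the other.

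**Joint draw of eight hubs, stratified by urban-rural only.** Each stratum has 4!/(2!·1!·1!) = 12 arrangements, and either stratum can hold the two MFL hubs: 2 × 12 × 12 = 288 allocations. Each stratum has two hubs per county, so:

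- Both control hubs in one county: 2 × (1/2 × 1/2) = 1/2 = 50%.
- All three MFL hubs in one county: 2 × (1/6 × 1/2) = 1/6 = 17%. The same holds for usual programme.
- MFL and usual programme wholly in opposite counties: 2 × (1/6 × 1/6) = 1/18 = 5.6%.
- MFL or usual programme wholly in one county: 1/6 + 1/6 − 1/18 = 5/18 = 27.8%.
- At least one arm wholly in one county: 160/288 = 55.6% by full enumeration. In 80 of these 160 (27.8% of all allocations) only the control arm is affected.
- MFL and control wholly in opposite counties: 32/288 = 11.1%.

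**Sensitivity to the assumed split.** With no stratification there are 8!/(3!·3!·2!) = 560 allocations. The corresponding figures are 42.9% (controls), 14.3% (MFL), 5.7% (MFL and usual opposite) and 48.6% (any arm). The urban-rural stratum does not reduce the imbalance.

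**Separate draws by county.** Nothing can be computed, because arm numbers per county are not stated. With 2/1/1 in one county and 1/2/1 in the other, no arm can lie wholly in one county. Each county has only two urban and two rural hubs for three arms, so the stated stratification would need a further rule to work within a county.

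**Daylight.** Assuming a latitude of about 52.6°N (not in the article) and follow-up windows 3 and 6 months after each baseline window, mean day length in hours is:

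| | Baseline | 3 months | 6 months |
|---|---|---|---|
| Limerick | 16.3 | 12.6 | 8.1 |
| Clare | 12.6 | 8.1 | 11.8 |

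- Change to 3 months: Limerick 12.6 − 16.3 = −3.7; Clare 8.1 − 12.6 = −4.5; difference 0.8 h.
- Change to 6 months: Limerick 8.1 − 16.3 = −8.2; Clare 11.8 − 12.6 = −0.8; difference 7.4 h.

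The article gives no relation between daylight and MVPA, so these hours cannot be turned into minutes of activity.

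**Timing.** One draw after the last Clare baseline visit could fall as late as October. The Limerick programmes last 8 or 12 weeks after a May-July baseline, and the Discussion expects some follow-up in September. One trial-wide draw after all baseline data cannot meet that calendar.

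**With county balance added.** Of the 288 allocations, 128 also give each county one control hub and a 2:1 or 1:2 split of MFL and usual programme. None puts an arm wholly in one county. The gap in the share of Limerick hubs is then 1/3 for MFL against usual programme and 1/6 for MFL against control. A sequential draw is possible: all 24 such Limerick arrangements leave valid Clare arrangements (16 leave six, 8 leave four; 16 × 6 + 8 × 4 = 128).

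**The case against.** This is a feasibility trial. Its primary outcome is whether MVPA can be measured, hypothesis tests and regression are declared exploratory, and no progression criterion compares arms. The seasonal effect is disclosed, and the strata were chosen after expert discussion. All of that stands and limits the harm.

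The wording also allows milder readings. The word 'only' in the Discussion contrasts urban-rural with social status, age and gender, and the hubs are then listed county by county, so stratification within county may have been intended. Baseline completion may be meant per hub or per county. Both readings are possible; neither is stated.

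Four stronger conclusions are tempting and are not supported:

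- A reader might take 56% as the plan's actual risk. It applies to one joint draw with an assumed split, and the calendar suggests that the counties may be drawn separately.
- A reader might convert daylight into a spurious MVPA difference. The documents give no slope, and the largest contrast needs two arms fully split by county, which is uncommon even under a joint draw.
- A reader might say that season could never be separated from arm afterwards. MFL and usual programme both span both counties in 100 − 27.8 = 72.2% of the joint allocations, so a within-county comparison usually remains. Daylight falls and then rises in Clare, which helps to separate it from time since start.
- A reader might call the randomisation rule unworkable. It conflicts with the calendar only when read for the whole trial.

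**Conclusion.** The point holds as an inexpensive improvement to the design. County determines season, the stated stratum carries no information on county, and the planned correlation would not remove season from an arm comparison. Under a joint draw, some arm lies wholly in one county about as often as not (56%, or 49% without stratification), most often the control arm. Under separate draws the risk is unknown, because the arm numbers per county are missing. For change from baseline the exposure is mainly at 6 months (about −8 h of daylight in Limerick against about −1 h in Clare) and small at 3 months (under 1 h difference). The daylight figures rest on an assumed latitude and on follow-up windows derived from the baseline windows. The damage is confined to exploratory between-arm estimates and retention comparisons.

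**What to change.** 1. Draw each county as its own block once that county's baseline is complete, and amend Randomisation process to say so.
2. Restrict the draw so that each county has one control hub and a 2:1 or 1:2 split of MFL and usual programme, balanced on urban-rural across the trial. The 128 qualifying allocations can be listed in advance, with the Clare draw made from those compatible with the Limerick result.
3. Report exploratory arm comparisons adjusted for county by visit, or for daylight hours at each visit, instead of relying on the correlation.
4. If randomisation has already taken place, report the arm-by-county layout, make the adjusted comparison, and state season as a limitation wherever an arm lies in one county.

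The cost is fewer possible allocations (128 instead of 288) and one between-hub degree of freedom, which matters somewhat with eight hubs. Once Limerick is revealed, Clare's arm numbers and the stratum of its control hub are also determined, so the restriction rule should be kept from those recruiting and testing in Clare. No extra hubs, participants or visits are needed.
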